### Sample size calculation

We assume that the rates of ‘Successful bone regeneration’ as a primary endpoint are commonly 95% in the two groups based on our clinical pilot study [14]. The non-inferiority margin is set to be 15.0% as a clinically acceptable difference.

With 83 sites per group, there was 80% power to examine the non-inferiority of the BM-MSCs group relative to the control group under the assumption of a two-sided significance level of 5.0% and an allocation ratio of 2: 1 to the BM-MSCs group or control group.

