### Statistical analysis

All the analysis is based on an intention to treat principle. The primary analysis is to estimate the differences in the rate of ‘Successful bone regeneration’ and its 95% confidence interval (CI) based on the Clopper-Pearson method. The non-inferiority of the BM-MSCs group relative to the control group is evaluated based on whether the lower limit of the 95% CI exceeds the non-inferiority margin of 15%. The descriptive statistics for continuous variables and frequency and proportion for categorical variables are calculated. The time-to-event data are summarized by using the Kaplan-Meier method. All the statistical tests use a two-sided *p*-value. *P* < 0.05 is considered to be statistically significant. All the statistical analyses are performed by using the SAS version 9.4 (SAS Institute, Inc., Cary, NC, USA), and performed according to the statistical analysis plan.

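### The interval that decides non-inferiority is assigned to Clopper-Pearson, a one-proportion method that does not define a confidence interval for a difference in rates

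*Protocol article*

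**What the plan says.** Under Statistical analysis, the protocol article sets the estimand: "The primary analysis is to estimate the differences in the rate of" successful regeneration. The same sentence continues with "its 95% confidence interval (CI) based on the Clopper-Pearson method". The next sentence gives the decision rule: non-inferiority depends on whether "the lower limit of the 95% CI exceeds the non-inferiority margin of 15" per cent. That section also says that analyses follow a statistical analysis plan, which is not shown.

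Under Sample size calculation, success rates "are commonly 95% in the two groups based on our clinical pilot study", and "The non-inferiority margin is set to be 15.0% as a clinically acceptable difference". With a two-sided 5% level and "an allocation ratio of 2: 1 to the BM-MSCs group or control group", the article states that "there was 80% power to examine the non-inferiority of the BM-MSCs group relative to the control group". Overall design and objective gives the arm sizes as 55 and 28 regions, 83 in all.

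**The concern.** Clopper-Pearson inverts the tails of a single binomial distribution. It gives limits for one rate and none for the difference between two independent rates. The sentence cannot be saved by taking the interval to be that of each arm's rate, because the next sentence compares its lower limit with a margin on the difference. Only an interval for the difference can be used that way.

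The named method therefore does not produce the number on which the primary conclusion rests. The analyst has to supply a rule for combining the two arms' limits, and the article gives none. If the possible rules differ in power, or reach different verdicts on the same data, the primary test is not fixed by the text.

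**Working it through.** **Inputs.** Arm sizes 55 (BM-MSCs) and 28 (control), from Overall design and objective. True rates of 95% in both arms, margin 15 points, two-sided 5% (2.5% one-sided), 80% power and 2:1 allocation, from Sample size calculation. Two conventions apply throughout: the margin is read as -15 points on BM-MSCs minus control, and sites are treated as independent.

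**1. The plan's own figure.** The unpooled normal formula for the control arm is (1.960 + 0.842)² × 0.95 × 0.05 × (1 + 1/2) / 0.15² = 7.849 × 0.07125 / 0.0225 = 24.9. That is 25 + 50 = 75 sites, not 83. The Farrington-Manning approximation gives 30 + 60 = 90, and 77.8% power at 55:28. An exact unconditional score test with size at most 2.5%, enumerated at 55:28, has 81.0% power. So 83 with 80% power is reproduced as a total under an exact two-sample method.

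**2. Clopper-Pearson limits for one arm.** For x successes in n, the lower limit L is the 2.5% quantile of Beta(x, n - x + 1). The upper limit U is the 97.5% quantile of Beta(x + 1, n - x). Neither formula involves a second arm.

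**3. Two ways to build a lower limit for the difference d = p_T - p_C.**

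- Subtraction: L_T - U_C.
- Square-root rule (Newcombe-type): d - √[(p_T - L_T)² + (U_C - p_C)²].

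**4. Operating characteristics.** All 56 × 29 outcomes were enumerated, and binomial probabilities were summed over those whose lower limit is above -15 points.

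| Lower limit | Power, 95% v 95% | One-sided error, 80% v 95% | Maximum error along the margin |
|---|---|---|---|
| Clopper-Pearson, subtracted | 57.9% | 0.2% | 1.1% |
| Clopper-Pearson, square-root rule | 81.0% | 2.3% | 2.4% |
| Exact unconditional (score) | 81.0% | 2.3% | 2.4% |
| Score (Farrington-Manning / Miettinen-Nurminen type) | 86.4% | 2.5% | 3.0% |
| Newcombe (Wilson limits) | 86.5% | 2.8% | 3.1% |

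Every outcome that passes by subtraction also passes by the square-root rule. The two therefore disagree in 81.0 - 57.9 = 23.1% of trials at the planned rates.

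These figures move in steps because the data are discrete. One more BM-MSCs site (56:28) lifts the subtraction reading to 70.2%. At exact 2:1 allocation, that reading first reaches 80% power at 74 + 37 = 111 sites (82.5%).

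**5. One data set, two verdicts.** Take 52/55 v 27/28, so d = 0.9455 - 0.9643 = -0.0188. Here L_T = 0.8488 and U_C = 0.9991.

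- Subtraction: 0.8488 - 0.9991 = -0.1503, which fails the margin.
- Square-root rule: -0.0188 - √(0.0967² + 0.0348²) = -0.0188 - 0.1028 = -0.1216, which passes.

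On the same data the score limit is -12.0% and the Newcombe limit -11.7%; both pass.

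**The case against.** The strongest reply is that subtraction is the least likely reading. It gives 58% power against a stated 80%, whereas the square-root rule, or a loose use of the name for an exact two-sample method, gives about 81% and fits. This stands as an argument about what was probably meant. A reader might infer from the 58% that the planned test is badly conservative, or that subtraction is the only literal use of the method. The article supports neither: it names no combining rule, and an interval built from Clopper-Pearson limits by the square-root rule is equally based on that method. With subtraction set aside, the readings are also close. The square-root and Newcombe verdicts differ in about 5% of trials at the planned rates, and the flip example misses the margin by only 0.03 points.

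A reader might also infer that, in an open-label trial, the rule would be chosen after the outcomes are known. The documents do not show that. The article refers to a statistical analysis plan, which may settle the rule beforehand. This does not clear the sentence itself, because the article does not leave the method to that plan. It names one, of the wrong kind.

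Clopper-Pearson's assumption of independent sites is no special fault either, since unadjusted Newcombe and score intervals share it. Finally, the article calls the study exploratory and says that secondary endpoints will be weighed as well. That lowers the stakes, but non-inferiority is still declared from this one limit.

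**Conclusion.** The concern holds as a wrong specification: a one-proportion method is named for the interval of a difference, and that interval decides non-inferiority. The power of an interval built from Clopper-Pearson limits runs from about 58% to about 81% depending on a rule the article does not state, and only the upper figure agrees with the stated 80%. Heavy conservatism belongs to the subtraction reading alone.

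The figures assume 55 and 28 independent sites, 95% success in both arms and a margin read as -15 points. Correlation of outcomes within a patient would change them for every method listed.

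**What to change.** Under Statistical analysis, replace Clopper-Pearson for the difference with one named two-sample interval, and confirm that the statistical analysis plan says the same. An exact unconditional interval keeps one-sided error below 2.5% in the enumeration and matches the stated power. Miettinen-Nurminen or Newcombe gains about 5 points of power, but error can reach about 3% at this size, and the text should acknowledge that. Clopper-Pearson can stay for describing the rate within each arm. The power statement should then name the same method.

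The cost is one sentence in each document and a rerun of the sample size calculation, before outcome data are analysed. Whichever interval is chosen must also allow for segments clustered within patients. That is a separate point and needs more than a change of name, with at most 29 patients, 10 of them controls.

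Stratifying the interval is optional and not needed to correct this error.

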## Methods/design

### Overall design and objective

The primary objective of this clinical study is to evaluate the efficacy and safety of bone regeneration therapy using tissue engineering materials including BM-MSCs in patients with maxillomandibular bone defects resulting from maxillofacial injury, or tumor/cyst removal. The TEOM study is an open-label, single-center (Nagoya University Hospital, Japan), randomized controlled study involving a total of 83 regions (BM-MSCs group: control group = 55 regions: 28 regions) by the Fédération Dentaire Internationale numbering system in patients with large jawbone defects. Maximum patient number is 29 (BM-MSCs group: control group = 19 patients: 10 patients) with at least 3 defect segments per patient thereof. A flow diagram of the TEOM study is shown in Fig. 1. The primary endpoint of this study is the rate of procedure sites with successful bone regeneration that satisfies both of the following definitions; i) CT value is at least 400, and ii) Bone height is over 10 mm. We decided as a specific hypothesis that the rate of patients who fulfil the primary endpoint criteria is similar in both groups, and the non-inferiority margin is 15.0%. Additionally, we will consider whether or not secondary endpoints in the BM-MSCs group will be superior to those in the control group.

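### The primary non-inferiority rule lacks a minus sign: as written, BM-MSCs must beat control by more than 15 points, although 95% success is assumed in both groups

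*Protocol article*

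**What the plan says.** The primary analysis in the Statistical analysis section is to "estimate the differences in the rate of" successful bone regeneration, with a 95% confidence interval. Non-inferiority of BM-MSCs to control is then "evaluated based on whether the lower limit of the 95% CI exceeds the non-inferiority margin of 15" per cent. This is the article's only decision rule for the primary endpoint.

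The Sample size calculation section gives the margin without a sign: "The non-inferiority margin is set to be 15.0% as a clinically acceptable difference". It takes the success rates "as a primary endpoint are commonly 95% in the two groups" and plans "under the assumption of a two-sided significance level of 5.0" per cent with "an allocation ratio of 2: 1 to the BM-MSCs group or control group". Overall design and objective gives "a total of 83 regions (BM-MSCs group: control group = 55 regions: 28 regions") and states the working hypothesis that the two groups have similar rates. The Abstract says the same. No section says which group is subtracted from which.

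**The concern.** Success is the favourable outcome, so non-inferiority means that BM-MSCs may fall short of control by no more than 15 points. With the difference taken as BM-MSCs minus control, the lower limit must therefore lie above -15. A lower limit above +15 would instead show that BM-MSCs is better by more than 15 points.

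This rule decides the primary conclusion. Read literally, a trial that turns out exactly as planned would fail. If the sign is corrected only once results are known, the threshold will appear to have moved by 30 points (from +15 to -15) in an open-label trial.

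**Working it through.** **Inputs from the protocol article.** Success rate 0.95 in each group; margin 0.15; two-sided 5%; power 80%; allocation 2:1 (Sample size calculation). Sites 55 and 28, total 83 (Overall design and objective). Sites are treated as independent throughout, except where stated.

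**1. The plan's own sample size.** The unpooled normal approximation, with the limit at -15 points, gives for the control group

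n = 0.95 × 0.05 × (1 + 1/2) × (1.960 + 0.842)² / 0.15² = 0.0475 × 1.5 × 7.849 / 0.0225 = 24.9.

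The total is 3 × 24.85 = 74.6, or 75 when rounded to 25 + 50. The stated 83 is not reproduced. A Farrington-Manning calculation gives 88. Only 74.6/0.9 = 82.8 rounds to 83, and that needs a 10% loss that the article does not state. This mismatch is a separate matter, as is the Sample size section attaching 83 to each group rather than to the total. What matters here is that all of these calculations use the limit at -15.

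**2. Both directions of subtraction.**

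| Difference | Meaning of lower limit > +15 | Correct non-inferiority rule |
|---|---|---|
| BM-MSCs minus control | BM-MSCs better by more than 15 points | lower limit > -15 |
| Control minus BM-MSCs | BM-MSCs worse by more than 15 points | upper limit < +15 |

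Neither direction makes the written sentence a non-inferiority rule.

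**3. Ceiling on the true difference.** With control at 95%, the largest possible true difference is 100 - 95 = +5 points. That is 10 points below the written threshold.

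**4. Normal approximation at 55:28, 95% in both groups.** SE = √[0.0475 × (1/55 + 1/28)] = 0.0506, and 0.15/0.0506 = 2.965.

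- Lower limit > -15: Φ(2.965 - 1.960) = Φ(1.005) = 84.2%.
- Lower limit > +15: Φ(-2.965 - 1.960) = Φ(-4.925) = 4 × 10⁻⁷.

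**5. Exact enumeration of all binomial outcomes at 55:28.** Probability of meeting each rule:

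| True rates (BM-MSCs / control) | Limits | > +15 (as written) | > -15 |
|---|---|---|---|
| 95% / 95% | Newcombe | 5 × 10⁻⁷ | 86.5% |
| 95% / 95% | Wald | 1 × 10⁻⁷ | 90.1% |
| 95% / 95% | Wald, continuity-corrected | 4 × 10⁻⁸ | 78.4% |
| 95% / 95% | Clopper-Pearson limits subtracted | 3 × 10⁻⁹ | 57.9% |
| 100% / 95% | Newcombe | 6 × 10⁻⁶ | not needed |
| 95% / 80% | Newcombe | 2.0% | not needed |

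Score limits give 86.4% for > -15 at 95% in both groups.

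**6. What data would satisfy the written rule.** Suppose all 55 BM-MSCs sites succeed.

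- Control could then have at most 19/28 successes (68%, Newcombe) or 18/28 (64%, Wald). If the true control rate is 95%, the chance of so few is 6 × 10⁻⁶ or 6 × 10⁻⁷.
- With 55/55 against 27/28, the lower limit is only 1 - 0.964 - 1.960 × √(0.964 × 0.036/28) = 0.0357 - 0.0687 = -3.3 points (Wald), or -3.6 points (Newcombe).

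**The case against.** The strongest reply is that nobody would be misled. The sentence itself says that it assesses non-inferiority, the margin is described as an acceptable difference, equal rates are assumed, and margins are often quoted as unsigned magnitudes. Read together, these leave only one workable rule, a lower limit above -15. The Statistical analysis section also defers to a separate analysis plan, which may state the rule correctly.

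Much of this stands. A dropped minus sign is the likely cause. The unsigned margin in the Sample size calculation section is normal usage and not itself an error; it is evidence of what was meant. Nothing can be said about the content of the analysis plan, which is not shown. But the article does not leave the rule out for the analysis plan to supply. It states the rule, and states it wrongly. A correct analysis plan would then conflict with the published protocol on the primary decision.

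A second reply is that the 86% comparison is soft. It rests on Newcombe limits, whereas the article names Clopper-Pearson, and on independent sites, whereas the design has at most 29 patients with at least three segments each. This also stands. The figure runs from 78% to 90% across the difference intervals tried, and is 57.9% if separate Clopper-Pearson limits are subtracted. With about three sites per patient and assumed intraclass correlations of 0.2 and 0.5, the Newcombe figure falls to about 83% and 80%. None of this affects the sign: the probability under the written rule stays close to zero throughout.

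**Conclusion.** The concern holds. The stated decision rule for the primary endpoint is not a non-inferiority rule under either direction of subtraction, and it contradicts the article's own hypothesis, margin and sample size assumption. Under 95% success in both groups with 55 and 28 independent sites, the chance of meeting it is below one in a million, against about 86% (Newcombe) for the evidently intended rule.

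The rule is strictly out of reach for the true difference, which cannot exceed +5 points when control is at 95%. For observed data the probability is negligible rather than exactly zero. The sign error itself depends on no interval method or clustering assumption; only the size of the comparison figure does. Because this sentence decides the primary conclusion, it must be corrected, even though the intent can be guessed.

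**What to change.** In the Statistical analysis section, define the difference as the success rate in the BM-MSCs group minus that in the control group. State that non-inferiority is concluded if the lower limit of the two-sided 95% confidence interval for this difference is greater than -15 percentage points. For consistency, the Abstract, Overall design and objective and Sample size calculation sections could refer to the same signed margin, and the analysis plan should be checked to confirm that it carries the same rule.

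The cost is about one sentence, with no change to design, sample size or data collection. It should be made as a dated correction before outcome data are compared between groups.

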### Audit

A systematic and independent examination were conducted according to the protocol, standard operating procedures, and the applicable regulatory requirements.

## Discussion

Recently, there have been many reports of cell therapy in tissue engineering approaches, although, these evaluations have not been established clearly. Our basic research revealed that cultured BM-MSCs improved the volume and hardness of regenerative bone in a dog model of bone defects [10–12]. Although these promising basic research results drove us to implement clinical studies, our clinical studies were case series or case reports in patients with relatively small atrophy or defects [10, 13–19]. In a systematic review of a regenerative approach to edentulous maxilla [22], it was concluded that ‘clinical trials assessing meaningful outcomes, involving larger populations, and with longer follow-up are warranted to discern the effectiveness of the achieved results compared with a valid control.’ In this review, two reports are cited as randomized controlled trials in patients with severe vertical or combined defects, but these clinical study designs both were the split-mouth design in the comparison effect between PRP in combination with autologous bone and autologous bone alone [23, 24]. Accordingly, there are no randomized controlled trials of cell therapy in severe atrophy or defects in the jawbone as far as we know. Therefore, we intended to implement this trial as the randomized control trial for evaluating the efficacy and safety of BM-MSCs in patients with large maxillomandibular bone defects.

As above, we constructed the rationale of the main design as a randomized controlled clinical trial for maxillomandibular bone defects based on our previous research [10–19]. Then, we discussed the design of the investigator-initiated clinical study (the TEOM study) in a consultation meeting with MHLW. As a result of a series of discussions, the Advanced Medical Treatment Council of the MHLW accepted our proposal.

### Ethics approval and current status on this trial

This study protocol is in accordance with the Declaration of Helsinki [25], the ‘Act on the Safety of Regenerative Medicine’ in Japan, and notifications of the Advanced Medical Care program from MHLW. Personal information management is in accordance with the protection regulation in Nagoya University. The compensation and/or treatment is available to the subject in case of the trial-related adverse event in accordance with the compensation regulation in Nagoya University.

The protocol of this trial was approved by the Certified Special Committee for Regenerative Medicine of The Japanese Association for the Promotion of State-of-the-Art in Medicine in November 2015 (No. PB4150004), however in January 2017 we changed the reviewing ethics committee to Nagoya University. Moreover, in December 2015, a clinical trial notification was accepted by the Advanced Medical Treatment Council of the MHLW (No. 1218–3). Protocol modification is also reviewed by these committees. The first patient completed registration in May 2016 and received transplantation of tissue engineered materials in July 2016. The TEOM study has currently enrolled 28 segments in 4 patients and is still recruiting patients from the Nagoya University Hospital. We are planning to enroll 83 regions as the full analysis set. The limit of enrollment will be January 2020, and the planned study end is July 2022.

## Conclusion

We present herein the overall design of this open-label, single-center, randomized controlled study to evaluate the efficacy and safety of tissue engineered osteogenic materials in bone defect patients. In this article, we provide the key considerations regarding the overall study design, selection of subjects, registration, application of tissue engineered materials, response variables (endpoints), number of subjects and statistical analysis. When this trial is completed or prematurely terminated, the clinical study reports are prepared according to the standard operating procedure, and submitted in peer review journal.

The TEOM study is the first randomized controlled clinical trial of a regenerative treatment for patients with maxillomandibular bone defects using BM-MSCs derived using our cultivation methods. We will evaluate efficacy and safety in this trial to provide an exploratory basis for the clinical meaning of additional cells in bone augmentation.

## Abbreviations

BM-MSCs: Bone marrow-derived mesenchymal cells
CI: Confidence interval
CT: Computed tomography
MHLW: Ministry of Health, Labour and Welfare
PRP: Platelet-rich plasma; QOL: quality of life
β-TCP: Beta-tricalcium phosphate
